### 3.3 Experimental results

The experimental results with the single active ingredients are listed under main function in the table below. First data show that a combination of GOS/FOS with AOS may have an additive/synergistic effect in animal trials on balance of the TH1/TH2 system.

| Ingredient | Source             | Main Function                                                                              | Concentration / 100 ml | Composition                 |
|------------|--------------------|--------------------------------------------------------------------------------------------|------------------------|-----------------------------|
| GOS/FOS    | Lactose / Chicoree | TH-Cell-Balance, IgE reduction
Total Gut Flora
Promotion of Bifidus
Anti-Pathogen | 0.68 g                 | GOS:FOS = 9:1               |
| Acidic OS  | (Citrus) Pectin    | TH-Cell-Balance
Gut Barrier
Reduction of pH
Anti-Pathogen                         | 0.12 g                 | Pectin-
Oligosaccharides |

### 3.4 Clinical results

Beside the various studies with GOS/FOS cited in the text under para 3.1 first interim data indicate that GOS/FOS have in addition to the *anti-pathogenic* effect also an *anti-infective* effect. In a first pilot trial it could be shown that the number of episodes of respiratory infections in the postnatal period was decreased in group of healthy term infants fed a GOS/FOS supplemented formula when compared to a group fed standard starting formula.

In term infants at risk for allergies, first data indicate also an effect of GOS/FOS on the immune system with regard to *reduction of IgE levels* in the blood. IgE is strictly related to allergy.

For AOS, a first study on the nutritional efficacy was performed in healthy term born infants (n=15 per group) during the first two months of life with AOS concentrations similar to those found in human milk. AOS as isolated supplement or in combination with GOS/FOS was well tolerated and no indication of a group difference for crying, regurgitation or vomiting was found. In no case any side effect occurred. Weight and length gain was normal in all infants. Significant prebiotic effects on stool pH and stool consistency were observed in the AOS group compared to the control group, however, the effect was not as strong than observed for the group fed the formula supplemented with the combination of GOS/FOS and AOS. As there was no effect of the AOS on the counts of bifidobacteria in the stools, a prebiotic effect different from a bifidogenic effect is indicated.

 Bruzzese B, Guarino A et al. Quaderni di Pediatria 2004; 3:98

 Moro G et al., presented at the 21st Int Symp Neonat Int Care Milano, Nov 2004

 Fanaro S, Jelinek J, Stahl B, Boehm G, Vigi V. Submitted to J Pediatr Gastroenterol Nutr

Also in another study (publication in preparation) with a higher number of healthy term infants (n=27 per group) at an age of 1 week up to 3 months at recruitment and an observation period of about 4 months, all infants grew similar when being fed a formula supplemented with GOS/FOS or a combination of GOS/FOS and AOS compared to a non-supplemented control group (due to the different age at study entry infants were followed up by calculation of z-scores from the Eurogrowth study to adjust for age and gender). Also for the other parameters investigated, e.g. stool consistency, occurrence of diarrhoea, regurgitation or other health complaints no peculiarities occurred and in no case a group difference could be observed.

#### **4. AIM OF THE STUDY**

The aim of the study is to investigate whether formula feeding (IF/FOF) supplemented with a mixture of immunomodulating neutral and acidic oligosaccharides is able to reduce the incidence of infectious illness in healthy term born infants during the first year of life.

#### **5. WORKING HYPOTHESIS**

It is hypothesised that dietary intervention with a formula (IF/FOF) supplemented with a mixture of immunomodulating neutral and acidic oligosaccharides will significantly reduce the incidence of febrile infectious diseases in healthy term born infants during the first year of life when compared to control infants receiving the placebo formula as indicated by

- primary parameter: number of febrile episodes (peak rectal temperature at least 38.5 °C) and
- secondary parameter: symptoms of infection (cough, wheeze, runny nose, vomiting, diarrhoea etc.) and their duration.

## 6. STUDY PARAMETERS

### 6.1 Primary outcome parameter

The primary outcome parameter is the number of febrile episodes (peak rectal temperature at least 38.5 °C) during the first year of life.

The febrile episode is considered as finished if the child is again without fever and other symptoms. Another febrile episode is considered as new period if the fever occurs at least three days after the stated time of recovery from a previous episode.

### 6.2 Secondary outcome parameters

As secondary outcome parameters symptoms of illnesses indicating a viral or bacterial infection (cough, wheeze, runny nose, vomiting, diarrhoea, others) as recorded in the diaries of the mothers.

The definition of such symptoms is as follows

- *Cough*: sudden expulsion of air from the lungs with a noise that clears the air passages
- *Wheeze*: breathing with an abnormal (e.g. husky or whistling) sound mostly due to difficult respiration by narrowed airway passages
- *Runny nose*: nasal discharge of any mucus-like material coming out of the nose (Rhinorrhea)
- *Vomiting*: forcing the contents of the stomach up through the esophagus and out of the mouth
- *Diarrhoea*: at least three loose-to-watery bowel movements in a 24 h period that exceeded the child's usual daily stool frequency by two or more stools and perceived as diarrhoea by the mother (WHO definition: "passage of loose or watery stools at least three times in a 24 h period"; emphasis on importance of change in stool consistency rather than frequency; usefulness of parental insight in deciding whether children have diarrhoea or not; see WHO: The treatment of diarrhoea: a manual for physicians and other senior health workers, WHO/CDR/95-3. Geneva: World Health Organisation, 1995)

Severity of illness episodes is explored by means of parameters such as

- Duration of illness symptoms (number of days; illness period is considered as finished if the child is again without symptoms and shows a normal activity level; after recovery, another illness is considered as new period if the symptoms occur at least three days after the stated time of recovery from a previous episode).
- Medication required as therapy (paracetamol, antibiotics, others) and their duration of use (number of days)
- Number of visits to hospital/practitioner
- Information if a physician has been visited who confirmed a diagnosis of infection
- Absence from day-care due to illness (number of days)
- Necessity of hospitalisation and respective duration (number of days)

Occurrence of allergic symptoms with focus on the skin (atopic dermatitis) will be checked during the clinical examinations:

- Criteria for diagnosis: typical morphology and distribution, pruritus (sign of scratching), chronicity (duration at least 14 d and/or chronically relapsing)
- Severity to be scored according to SCORAD

The skin should also be checked during this examination for eczema and urticaria.

Further secondary parameters are those gained through analyses of biological samples, i.e. stools and blood. As biochemical blood/plasma parameters of immune status, at least in a subgroup of infants, including vaccination response, following parameters of humoral or cellular status or mediators will be checked:

- Plasma antibodies: IgG, IgE, specific antibody titres (as response to vaccination; as allergy markers: antibodies against cow's milk, cat, soy, wheat and dust mite allergens)
- Lymphocyte subpopulations
- Cytokines (after ex vivo stimulation)

As stool parameters of gut health, immune status and inflammation, at least in a subgroup of infants, the following parameters will be analysed:

- CFU/g stools of Bifidus sp., Lactobacilli sp., and pathogenic micro-organisms
- faecal pH
- faecal sIgA

### **6.3 Safety parameters**

As anthropometric parameters will be measured:

- Body weight and crown-heel body length
- Occipito-frontal head circumference
- Mid-upper arm circumference
- Skinfolds (triceps and subscapular)

Parameters of acceptance, tolerance and gastrointestinal discomfort are

- Number of feedings / intake
- Regurgitation/reflux: spitting up (mild, effortless), possetting (moderate), vomiting (severe, forceful)
- Stool frequency; stool consistency; stool colour
- Flatulence (excessive air/gas in the intestine passed through the rectum); cramps (unpleasant sensation caused by abdominal contraction); colics (intermittent attacks of abdominal pain when the baby screamed and drew up his/her legs but was well between episodes)
- Nappy rash (redness of the skin confined to the area covered by the nappy)

## **6.4 Possible confounding factors**

### **6.4.1 Obstetric, medical and social data**

- Maternal factors: age, parity, social class, height, smoking habit, marital stage, puerperal illness, previous medical illness
- Paternal and social factors: age, social class, number of rooms in the house, living conditions (urban / rural), smoking habit
- Infant factors: sex of child, date of birth (season!), birth weight, gestational age, mode of delivery (vaginally / caesarean section), Apgar score, neonatal jaundice, other illness before study entry, immunisation, number and age of siblings, illness in siblings, form of child care (home care, group care, day care centre)

### **6.4.2 Feeding pattern**

- Full breastfeeding: breastfeeding for more than 4 months without any introduction of supplements (formula feeds, cow's milk, solid feeds; some juice or water will be not counted as such) before end of 4th month of life
- Partial breastfeeding: breastfeeding for more than 4 months with introduction of supplements before end of 4th month
- Early weaning: discontinuation of breastfeeding before end of 4th month
- Formula feeding: first formula feeding before study entry (full formula feeding = bottle feeding from birth onwards = no breastfeeding at all); after study entry all formula given is study formula (IF/FOF); after the second month of life on full study formula feeding
- Mixed formula feeding: first formula feeding before study entry (but not on full formula feeding = partial breastfeeding); after study entry all formula given is study formula (IF/FOF); after the second month of life still partial breastfeeding

## **7. STUDY DESIGN**

The study will be performed as double-blind, placebo-controlled, randomised, prospective nutritional intervention study with a parallel group design.

## **8. STUDY DURATION**

- Per subject: Infants will be recruited until the infant's age of 8 weeks at the latest and will be followed until the age of 1 year.
- Recruitment phase: Subject inclusion in the five participating centres should be finalised within about one year.
- Total study duration: The total study will last for about 2 years in each center. It will start in June 2005 (first center) – August 2005 (last center) and the clinical part (last infant finished the study) will be completed presumably in August 2007 (last center).

## **9. STUDY GROUPS**

There will be two formula groups in the study:

- Group 1: Active Formula Group on full formula feeding after 2 months at the latest receiving a non-hydrolysed cow's milk based formula containing an immunomodulating mixture of neutral and acidic oligosaccharides. To avoid any immunological influence by other ingredients, the formula will not contain any other special supplementation such as probiotics, LCPUFA, or nucleotides.
- Group 2: Control Group on full formula feeding after 2 months at the latest receiving as placebo a standard non-hydrolysed cow's milk based formula with the same composition as the active formula but without supplementation of oligosaccharides. Other ingredients with suspected immunological influence will also not be supplemented, i.e. the only difference between the two formulas is the presence or absence of the supplemented mixture of neutral and acidic oligosaccharides.

The allocation to the two formula groups will be performed in a randomised way according to the stratified randomisation table (see annex) at study entry.

As non-randomised reference group, infants on full breastfeeding for at least 4 months will serve.

## **10. STUDY SUBJECTS**

### **10.1 Enrolment of subjects**

Mothers and their babies in the first 8 weeks of life from the region of Berlin, Groningen, Milan, Naples and Zurich will be informed about the study and asked to make up their mind if they would like to participate. E.g., a good time to approach the mothers is a routine visit to their hospital/practitioner for a routine investigation of their infants at the age of 4-6 weeks.

Those healthy term born infants fulfilling all requirements of inclusion but not exclusion criteria (see para 10.2 and 10.3) and whose parents after having been informed about the study and after having thought about it for at least some days have given their written consent for participation of their child in the study shall be enrolled. Each mother-infant couple will get a sequential number at study entry and keep that number throughout the study.

Study infants will be continuously recruited until a total number of about 500 formula infants per group will be reached (see para 10.4).

To comply with ethical standards not to influence breastfeeding mothers in any way to use an infant formula instead, mothers will only be asked to be recruited to a study formula group if they cannot/do not fully breastfeed their babies and had at least fed one bottle of formula before (mothers on full breastfeeding may only enter the reference group). Alternatively, mothers with healthy term newborns may be informed about the study (e.g. by a respective flyer containing also a contact telephone number), so that they actively can call back in case they would later on like to participate. Even after recruitment, mothers will not be influenced in any way in her decision to continue with breastfeeding as long as possible and therefore will also be followed within the study if she is able to breastfeed (at least partially) after their infants' age of 2 months (mixed-feeding group). Without ambivalence mothers will be told that breastfeeding offers clear advantages also by reducing the incidence of infections. She will not be told that infants will only be evaluated as formula infants in the per-protocol analysis if breastfeeding is finalized until the end of the second month of life.

By this procedure it should also be possible to exclude that the initial short breastfeeding period could be responsible for the outcome effect observed in the study. This assumption is supported by the results of the Dundee Breastfeeding Study which did not provide any evidence to suggest that brief periods of breastfeeding are sufficient to offer significant protection (Howie PW et al: Protective effect of breast feeding against infection. Br Med J 1990; 300:11-16). Nevertheless data on the duration and percentage of breastfeeding before and after study entry will be collected in order to test an influence as possible confounder also in the formula groups.

## 10.2 Inclusion criteria

- Healthy, term born infants (GA 37-42 weeks)
- with a normal birth weight (girls: 2.7-5.0 kg, boys: 2.9-5.2 kg),
- not older than 8 weeks of age when entering the study,
- not at high risk to develop an atopic disease (at least one parent or sibling with manifest atopic symptoms of hay fever, asthma or atopic dermatitis) which would require the feeding of an HA formula with hydrolysed protein according to current recommendations,
- and with no metabolic disorders requiring a special diet other than standard non-hydrolyzed IF/FOF.

## 10.3 Exclusion criteria

- Mothers suffering from hepatitis B, HIV or GBS (Guillain-Barré syndrome)
- Mothers taking antibiotics during breastfeeding
- Infants with known congenital diseases or malformations which would interfere with the study, e.g. gastrointestinal malformations, congenital or acquired immunodeficiency, etc.
- Study pre-feedings of the infants which could interfere with the study, e.g. non-cow's milk based formulas, HA formulas, probiotic formulas, etc.
- Infants with actual or previous illnesses which could interfere with the study (see CRF) Screening).

## 10.4 Randomisation

Randomization to one of the two formula groups will be performed directly after study entry of those mothers who have fed their infants at least one bottle of infant formula. Randomization will be performed stratified according to center. I.e., for each center a separate randomization list will be provided. All other potential confounders, such as obstetric, medical or social characteristics, will be checked and adjusted for in the final data analysis.

Time-balanced randomization will be performed with the software RANCODE (IDV, Gauting; seed numbers randomised by reaction time) with a random permuted block size of 4 so that after 4 infants each the same number of infants per formula group is reached. By this procedure the time influence (season etc.) is evenly distributed between the randomised group. An example of a randomization table is given in the annex.

## 10.5 Number of subjects and study power

Starting with 500 formula infants per group, it is assumed that about 35% will be lost for the per-protocol-analysis due to continuation of breastfeeding beyond the second month of life and further about 15% due to different dropout / withdrawal reasons so that 250 infants per formula group fully completing the study should be achieved.

With those 250 formula infants per group completing the study without violation of the protocol, a reduction of the mean number of febrile episodes by 1 which is considered as clinically relevant reduction (from 4.5 to 3.5, SD 3.5 episodes), compared to placebo can be proven with 93% power in an one-sided unpaired t-test or 89% in a two-sided unpaired t-test.

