### **11.5 Additional feeding recommendations**

Mothers are encouraged to breastfeed their infants for at least 4 months, preferably 6 months. The only substitute or supplement in case of insufficient breastfeeding is the randomised study formula. Parents are asked not to introduce weaning foods until their infants have reached the age of 4 months.

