## **18. WITHDRAWALS AND DROPOUTS**

Parents have the right to withdraw their infants from the study at any time for any reason. The investigator also has the right to withdraw subjects from the study for medical (or other sound) reasons. It is understood by all concerned that an excessive rate of withdrawals can render the study uninterpretable: therefore, unnecessary withdrawal of subjects should be avoided.

Refusal of specific study assessments or complete withdrawal from the study does not preclude a subject from subsequent evaluation. Unless they refuse, all subjects that have been randomised will be followed up.

If any subject fails to complete the study (withdrawal from the study, e.g. in case of revocation of parental consent, or dropout, e.g. in case of illness of study members\*) the reason should be specified in writing by the supervising physician. If parents decide to withdraw their child from the study without giving any reason this should also be stated. If needed for clarification of dropout or withdrawal reasons telephone interviews are to be planned.

For the intention-to-treat analysis, results will be reported for all subjects as randomised. For the per-protocol analysis, however, withdrawals, dropouts, and non-compliers will be excluded. Furthermore, formula fed infants with partial breastfeeding beyond four study weeks will be evaluated as separate groups (mixed feeding).

In case of >30% missing data of an infant the concerned subject will be excluded from the per-protocol evaluation (dropout because of missing data). The same is true if the specific feeding regimen for an individual is discontinued before the study end (dropout because of violation of feeding regimen). For identification of non-completers as possible non-responders, however, the protocols (CRFs) of those cases should also be carefully checked. Incidental feeding of small amounts of food different from the prescribed feeding regimen will not lead to exclusion (incidental intake of infant tea, glucose electrolyte solution for some hours, or else).

---

\* If patients fall ill during the study period, the main investigator will decide whether the disease requires withdrawal of the patient from the study. This will also depend on the type and dose of drug(s) provided for treatment.

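### Power is stated only for a per-protocol half of the randomised infants; the planned ITT analysis is neither named primary nor given any power

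*Protocol*

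**What the plan says.** Section 10.5 builds the sample size backwards from a per-protocol set. The base is given as "Starting with 500 formula infants per group". On losses, the section expects this: "about 35% will be lost for the per-protocol-analysis due to continuation of breastfeeding beyond the second month of life". Dropout and withdrawal are put at another 15%. Power of 93% (one-sided) or 89% (two-sided) is then given for "With those 250 formula infants per group completing the study without violation of the protocol", for a fall in mean febrile episodes "from 4.5 to 3.5, SD 3.5 episodes". Every column of the nQuery table uses 250 per group.

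Membership of the set is defined elsewhere:

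- Sections 12.3 and 12.9 remove formula infants who still receive breast milk after two months of age, and section 12.3 also removes those given other formula.
- Section 18 says: "For the per-protocol analysis, however, withdrawals, dropouts, and non-compliers will be excluded". It also removes infants with more than 30% missing data or a discontinued feeding regimen.
- Section 18 gives illness as an example of dropout, and its footnote adds that "the main investigator will decide whether the disease requires withdrawal of the patient from the study".
- Section 11.5 says: "Mothers are encouraged to breastfeed their infants for at least 4 months, preferably 6 months".

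An ITT analysis of all randomised infants by initial allocation is planned in the synopsis and in sections 12.3, 18 and 21.4. Section 21.4 describes it as additional to the per-protocol analysis. No section ranks the two or gives ITT power. The t-test example in section 14.1 names no population.

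**The concern.** The trial aims to show superiority. Randomisation protects a comparison only if infants are analysed as allocated, and here the comparison that carries the power keeps half of them, chosen by what happened after allocation. One way out of the set is illness, while the endpoint is a count of febrile illnesses, so the set can lose infants because of the outcome it measures. If such losses differ between arms, the per-protocol difference is biased, in either direction.

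The analysis that avoids this selection is already planned but has no stated standing. If the two sets disagree, the protocol does not say which one decides, and the choice could be made after the results are known. A separate SAP might settle primacy, but the protocol has itself tied the sample size to the per-protocol set, and that is what needs correcting.

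**Working it through.** **Inputs.** From section 10.5: 500 randomised per arm, losses of 35% and 15%, difference 1.0, SD 3.5. From section 14.3: alpha 0.05. Dilution and outcome-related exclusion rates are not in the protocol and are assumed below.

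**1. The plan's own figure.** Retention is 500 × (1 − 0.35 − 0.15) = 250. The standard error is 3.5 × √(2/250) = 0.313, so the effect is 1.0/0.313 = 3.19 standard errors. The noncentral t gives 89.0% two-sided and 93.9% one-sided. The stated 89% and 93% reproduce. The arithmetic is sound; the question is the population.

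**2. How far selection could move the per-protocol result.** Assume no true effect, mean 4.5 and SD 3.5 in both arms, and a chance of exclusion proportional to an infant's episode count. Excluded infants then have mean (SD² + mean²)/mean = (12.25 + 20.25)/4.5 = 7.22. If a fraction q is excluded this way, the rest have mean (4.5 − 7.22q)/(1 − q). The bias b is the difference between arms, and the two-sided error is 1 − Φ(1.96 − b/0.313) + Φ(−1.96 − b/0.313). Breastfeeding losses are taken as unrelated to outcome, and 250 per arm and SD 3.5 are held fixed.

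| q, one arm vs other | Remaining means | b | Type I error |
|---|---|---|---|
| 15% vs 15% | 4.02 vs 4.02 | 0 | 5.0% |
| 6.7% vs 3.3% | 4.31 vs 4.41 | 0.10 | 6.2% |
| 17% vs 13% | 3.94 vs 4.09 | 0.15 | 7.7% |
| 20% vs 10% | 3.82 vs 4.20 | 0.38 | 22.7% |

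The 6.7% vs 3.3% row treats one third of the 15% as illness-driven, split 2:1. The last row is extreme: it makes all of the 15% average outcome-related and also splits it 2:1.

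**3. ITT power.** Let adherent infants (50%) have an effect of 1 and the others a fraction f of it. The ITT difference is 0.50 + 0.50f. The table gives two-sided power at SD 3.5, for all 500 per arm and for 425 (0.85 × 500) with an outcome.

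| f | ITT difference | 500 per arm | 425 per arm |
|---|---|---|---|
| 0 | 0.50 | 61.7% | 54.8% |
| 0.25 | 0.625 | 80.5% | 73.9% |
| 0.5 | 0.75 | 92.3% | 87.7% |

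The 425 column keeps the same difference. If the infants without an outcome were all non-adherent, the difference would be somewhat larger (0.50/0.85 = 0.59 at f = 0), so that column is on the low side.

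To keep 89% power the ITT difference must be at least 0.705 (500 per arm) or 0.765 (425 per arm). That is f of at least (0.705 − 0.50)/0.50 = 0.41 or (0.765 − 0.50)/0.50 = 0.53.

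**The case against.** The strongest reply is that the set is smaller than the randomised one but not clearly biased. Of the 50 points lost, 35 are continued breastfeeding, which sections 12.3 and 12.9 settle at about 8 weeks of age. Enrolment runs up to 8 weeks, so many infants will have had little study formula by then. The product is blinded, and section 10.1 says mothers are not told the rule. If the formula has no effect on infection, illness-driven withdrawal should be about equal in the two arms. This stands as a reason to expect modest bias. It does not remove the bias: sections 3.1 and 3.4 report effects of the oligosaccharides on stool frequency, consistency or pH, so tolerance, and with it feeding choice and dropout, could differ by arm.

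Several stronger readings are tempting, but the documents do not support them:

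- **That much of the loss is due to illness and missing data.** Section 10.5 names only breastfeeding and dropout or withdrawal. Section 18 gives illness and missing data no share.
- **That the sickest infants will be withdrawn.** Section 18 leaves this to case-by-case decision, asks that unnecessary withdrawal be avoided, and follows all randomised infants unless they refuse.
- **That section 12.3 declares per-protocol primary by calling it intended.** The protocol uses that word elsewhere simply to mean planned.
- **That ITT is missing.** It is planned in four places.
- **That ITT power equals the stated 89%.** That holds only for particular dilution assumptions and complete outcomes.

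**Conclusion.** The point holds and should be corrected. The only powered superiority comparison uses 250 of 500 randomised infants per arm, selected after randomisation and partly through events related to the outcome. The analysis that respects randomisation has no stated primacy and no stated power.

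The direction and size of any bias are unknown. The range of 5% to about 23% type I error rests on assumed exclusion rates and one model. The upper end shows what could happen in an extreme case and is not a forecast; moderate imbalance gives about 6% to 8%. The 55% to 92% range of ITT power rests on assumed dilution, because the protocol gives no expected effect in infants who do not adhere.

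**What to change.** - In the synopsis and sections 10.5, 12.3 and 18, name the ITT analysis of all randomised infants as primary for febrile episodes, and per-protocol as supportive.
- In section 10.5, state ITT power with the assumed dilution and the number expected to have an outcome, for example as the range tabulated above.
- State that infants who leave early contribute their observed episodes and time at risk. Section 18 already provides for follow-up and for reporting as randomised. Section 14.1 needs a matching change, because its t-test on episodes per child takes no account of time observed. A count model with an offset for observed time would do this, and the power should then be checked under that model.
- Reconcile the mixed-feeding cut-off, which is two months of age in sections 12.3 and 12.9 but four study weeks in section 18. As written, the same infant can be inside or outside the per-protocol set.

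The cost is text in the synopsis and sections 10.5, 12.3, 14.1 and 18, with no change to recruitment unless the sponsor finds the diluted power too low. The downside is that the stated power becomes a range that can fall below 89%. If non-adherent infants gain nothing (difference 0.5), about 996 infants per arm with an outcome would be needed for 89%.

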### Statsol nQuery Advisor 5.0: Two group t-test of equal means (equal n's)

|                                                  | 1     | 2     | 3     | 4     | 5     | 6     | 7     | 8     |
|--------------------------------------------------|-------|-------|-------|-------|-------|-------|-------|-------|
| Test significance level, $\alpha$                | 0,050 | 0,050 | 0,050 | 0,050 | 0,050 | 0,050 | 0,050 | 0,050 |
| 1 or 2 sided test?                               | 1     | 2     | 1     | 2     | 1     | 2     | 1     | 2     |
| Group 1 mean, $\mu_1$                            | 4,500 | 4,500 | 4,500 | 4,500 | 4,500 | 4,500 | 4,500 | 4,500 |
| Group 2 mean, $\mu_2$                            | 3,500 | 3,500 | 3,500 | 3,500 | 4,000 | 4,000 | 4,000 | 4,000 |
| Difference in means, $\mu_1 - \mu_2$             | 1,000 | 1,000 | 1,000 | 1,000 | 0,500 | 0,500 | 0,500 | 0,500 |
| Common standard deviation, $\sigma$              | 3,000 | 3,000 | 3,500 | 3,500 | 1,500 | 1,500 | 2,000 | 1,500 |
| Effect size, $\delta =  \mu_1 - \mu_2  / \sigma$ | 0,333 | 0,333 | 0,286 | 0,286 | 0,333 | 0,333 | 0,250 | 0,333 |
| Power ( % )                                      | 98    | 96    | 93    | 89    | 98    | 96    | 87    | 96    |
| n per group                                      | 250   | 250   | 250   | 250   | 250   | 250   | 250   | 250   |

The assumption of at least 4.5 infection episodes is based on a study investigating the frequency, nature and severity of infections throughout the first 3 years of life in relation to three types of child care arrangement (home care, group care (2-6 children), and day care (> 6 children)). In this study it could be observed that the infection rates ranged from 4.5 episodes in the first year of life for infants with home care to more than 7 episodes for infants in day care centers (Wald ER et al. 1991. J Pediatr 118:509-514). Among the different illnesses, upper respiratory tract infection (URTI) was most prominent with 3.8 episodes for infants with home care up to 6.3 episodes for infants in day care centers in the first year of life.

The assumption of a standard deviation of maximum 3.5 episodes is based on the same publication in which the above described results were observed with standard deviations between 2 (home care) and 3 episodes (group care).

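### Section 10.5 states 93%/89% power for febrile episodes, but takes its mean of 4.5 and its SD from infection episodes, so the power is unsupported for the primary outcome

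*Protocol*

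**What the plan says.** Section 6.1 defines the endpoint: "The primary outcome parameter is the number of febrile episodes (peak rectal temperature at least 38.5 °C) during the first year of life". Section 5 keeps infection symptoms apart from it, as a "secondary parameter: symptoms of infection (cough, wheeze, runny nose, vomiting, diarrhoea etc.) and their duration".

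Section 10.5 sizes the trial on "a reduction of the mean number of febrile episodes by 1 which is considered as clinically relevant reduction (from 4.5 to 3.5", with "SD 3.5 episodes), compared to placebo", and concludes that 250 completers per group give "93% power in an one-sided unpaired t-test or 89% in a two-sided unpaired t-test".

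The text under the power table in the same section then explains the 4.5: "The assumption of at least 4.5 infection episodes is based on a study investigating the frequency, nature and severity of infections". It reports 4.5 episodes in the first year for infants in home care and more than 7 in day care. It adds that "upper respiratory tract infection (URTI) was most prominent with 3.8 episodes for infants with home care", so 3.8/4.5 = 84% of the home-care figure is upper respiratory infection. The SD is taken from the same publication, which reported SDs of 2 (home care) to 3 (group care); the protocol uses 3.5 as a maximum.

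**The concern.** Within one section the same 4.5 is called febrile episodes where the power is stated and infection episodes where it is justified. By the protocol's own definitions these are different outcomes. A runny nose with no fever is an infection episode but does not count towards the primary outcome. The protocol gives no rate of fevers of at least 38.5 °C, no fever criterion for the source figure, and no factor for turning one into the other. The planning mean, the SD and the target of one episode fewer therefore all lack support for the endpoint that the trial tests.

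This is the only justification of the sample size. If febrile episodes are much rarer than infections, one fewer per infant is a far larger relative effect than the 4.5-to-3.5 framing suggests, and at a low enough rate it cannot happen. A null result could then be read as coming from a trial with about 90% power when nothing in the protocol establishes that.

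**Working it through.** **Inputs from section 10.5.** Difference 1.0 (4.5 to 3.5), SD 3.5, n = 250 per group, alpha 0.05, unpaired t-test.

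**Step 1: reproduce the stated figure.** Noncentrality = difference / (SD × √(2/n)) = 1 / (3.5 × √(2/250)) = 3.194, with 498 degrees of freedom. Noncentral-t power is 93.9% one-sided and 89.0% two-sided. The stated 93% and 89% follow from the inputs, so there is no arithmetic error.

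**Step 2: what the absolute target means at a febrile rate.** Let f be the ratio of febrile episodes to infection episodes. The protocol does not give f; 0.2 to 0.5 is assumed. The control mean is 4.5f, and a fall of 1 is a relative reduction of 1/(4.5f).

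| f | control mean | fall of 1 as a share |
|---|---|---|
| 0.2 | 0.90 | 111% (impossible) |
| 0.3 | 1.35 | 74% |
| 0.4 | 1.80 | 56% |
| 0.5 | 2.25 | 44% |

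The fall is impossible once the mean drops below 1, that is for f below 1/4.5 = 0.22.

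**Step 3: power for a fixed relative reduction.** The fall from 4.5 to 3.5 is 1/4.5 = 22%. Holding that share, the difference is 4.5f × 0.222 = f. The SD of febrile counts is also unknown, so three assumptions are shown, each with a common SD and 250 per arm:

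- (a) Overdispersion carried over from mean 4.5 and SD 3.5. Negative binomial k = 4.5² / (3.5² − 4.5) = 20.25 / 7.75 = 2.61, and SD = √(m + m²/2.61), where m is the control mean.
- (b) Poisson: SD = √m.
- (c) SD in proportion to the mean: SD = 3.5f.

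| f | (a) SD | (a) two-sided | (a) one-sided | (b) SD | (b) two-sided | (c) two-sided |
|---|---|---|---|---|---|---|
| 0.2 | 1.10 | 53% | 65% | 0.95 | 65% | 89% |
| 0.3 | 1.43 | 65% | 76% | 1.16 | 82% | 89% |
| 0.4 | 1.74 | 73% | 82% | 1.34 | 91% | 89% |
| 0.5 | 2.05 | 78% | 86% | 1.50 | 96% | 89% |

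Example, (a) at f = 0.5: noncentrality = 0.5 / (2.046 × √(2/250)) = 2.73, which gives 77.8% two-sided.

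Two-sided power therefore runs from 53% to 96% over this grid, on both sides of the stated 89%.

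**The case against.** The strongest reply is that t-test power depends only on difference divided by SD. The 93%/89% statement is correct on its own terms, and nothing in the protocol shows that the trial is underpowered. That stands. A reader might infer from the mismatch that true power is below 89%; the documents do not support this. Under a Poisson SD it is above 89% at f = 0.4 and 0.5, and under a proportional SD it does not move.

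Several further points also hold:

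- The k of 2.61 rests on an SD that the protocol calls a maximum. The home-care SD of 2 is a variance of 4, below the mean of 4.5, so the source group for the 4.5 shows no overdispersion. Scenario (a) partly turns a safety margin into a loss of power.
- The 4.5 is a floor. Applied to 7 episodes (day care), f of 0.2 to 0.5 gives means of 1.4 to 3.5 and makes a fall of 1 a 71% to 29% reduction.
- The power table already has columns for a difference of 0.5. With SD 2.0 it prints 87% one-sided (80% two-sided on calculation), close to scenario (a) at f = 0.5. It labels that column as 4.5 to 4.0, however, and offers it for no febrile rate.
- The hypothesis is directional, and section 14.3 requires two-sided tests only where no direction is defined, so the one-sided figures are relevant.
- The sponsor calls an absolute fall of 1 clinically relevant. The 22% is a re-expression.
- Section 6.1 does not require a febrile episode to be an infection, so f is a ratio for planning and not strictly a subset fraction.

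None of this supplies a febrile rate. The margins on the mean and SD are margins on infection counts. Reading infection as loose wording for febrile does not fit section 5, which separates the two.

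**Conclusion.** The power statement is wrong as written. It attaches to febrile episodes a mean and SD that the protocol itself attributes to infection episodes. The fault is an unsupported planning input; the calculation from the printed figures is right.

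What is established is that 93%/89% has no support in the document for episodes of at least 38.5 °C. What is not established is the true power. The step 2 and step 3 ranges illustrate how much depends on the missing figures. They rest on an assumed febrile share of 20% to 50%, a base of 4.5, 250 per arm and, in step 3, a 22% relative reduction with the SD assumption named. The firmest consequence needs only the base of 4.5: at a febrile share below about 22%, one episode fewer cannot be reached.

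**What to change.** Change section 10.5 only; the synopsis gives a sample size but no power figure.

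1. Stop presenting 93%/89% as power for febrile episodes, and say that the 4.5 and its SD come from all infection episodes.
2. Give a planning mean and SD for episodes of at least 38.5 °C, with a source or as an openly assumed range.
3. Say whether the target is an absolute fall of 1 or a relative reduction.
4. Tabulate power at 250 per arm over that range, for the sidedness that will be used.

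Keep the sample size. The cost is one rewritten paragraph and one table, no extra infants and no change of design, and a power statement that may be less favourable than the present one.
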